### Statistical analysis

All statistical analyses will be carried out in intention-to-treat for effectiveness criteria. Sensitivity analyses will be carried out in per-protocol.

The demographic and baseline data will be described by randomization arm using descriptive statistics.

### Analyses of time-to-event data

The median duration of treatment and other survival rates will be estimated using the Kaplan-Meier method. Median survival will be described with their confidence intervals (one-sided statistical test of significance (*α* 5%)) in each of the arms.

Survival curves will be calculated by the Kaplan-Meier method and described using their medians and their 95% confidence intervals.

Multivariate Cox analysis will be conducted to identify factors potentially influencing survival.

All variables originally collected will be tested by univariate analysis. The variables with *P* ≤ 0.20 will be eligible in multivariate analysis.

No *P* value will be indicated, and the effect size of treatment will be assessed using the HR with its confidence interval.

### Analysis of HRQoL data

Descriptive analysis of HRQoL will be presented at baseline, at randomization, and every 6 weeks until the release of the study. HRQoL data will be resumed across TTD.

TTD is classically defined as the time from inclusion in the study to a first significant deterioration in a HRQoL score as compared to the baseline score with no further significant improvement, or death. Pre-specified targeted HRQoL dimensions will be general health status, physical functioning, fatigue, and pain.

TTD curves will be calculated by the Kaplan-Meier method and described using median and their 99% confidence intervals for the four target dimensions (and 95% confidence intervals for the other dimensions).

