## Methods/design

### Study design

SURF is a prospective, multicentre, randomized, open-label study in which patients are randomized between two medication schedules (standard schedule 4/2 vs experimental schedule 2/1) when a dosage adjustment (e.g., adverse event, patient request) of sunitinib is required (Additional file 1). Standard schedule 4/2 is defined as 2 periods comprising 4 weeks “on” with sunitinib followed by 2 weeks “off” without sunitinib. The experimental schedule 2/1 is defined as 2 periods comprising 2 weeks “on” with sunitinib followed by 1 week “off” without sunitinib.

At the inclusion, all patients start sunitinib at the recommended schedule 4/2 with sunitinib dosage of 50 mg once daily. When a dosage adjustment of sunitinib is required, patients will be randomized between two arms: one arm in which the dose of sunitinib is reduced to 37.5 mg once daily (standard schedule 4/2, arm 4/2) and one arm in which treatment is administered with a dose maintained at 50 mg once daily (experimental schedule 2/1, arm 2/1) (Fig. 1).

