#### Secondary endpoints

The key secondary objectives are measured to evaluate the efficacy and the safety of the experimental schedule 2/1 and are the following: are measured to evaluate the efficacy and the safety of experimental schedule 2/1:To estimate the PFS and OS of patients in each of the groups and in the overall population included in the studyTo describe the decision factors requiring dose adjustment leading to randomization to the dose of sunitinibTo estimate the time between the date of randomization and the treatment discontinuation (regardless of the cause) in the two treatment armsTo estimate the time to randomization defined as the delay between the date of initiation of treatment and the date of randomizationTo evaluate ORR, duration of response, and clinical benefit duration according to RECIST 1.1 criteria [11]To describe the toxicity before and after randomization according to NCI CTCAE version 4.0To describe dose modifications (dose reduction, interruption, or discontinuation) and to estimate the dose intensity in each treatment groupTo evaluate HRQoL from the initiation of treatment (before, during, and after randomization)To estimate time to HRQoL deterioration (TTD) in each of the groups and in the overall population included in the study

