### Study procedures and randomization

Patients candidate for first-line treatment with sunitinib and meeting the inclusion/exclusion criteria will be offered participation in the protocol. All the included patients will receive sunitinib 50 mg once daily with schedule 4/2 according to the marketing authorization indication.

When the investigator believes a modification of administration of sunitinib is necessary, the patient will become eligible for randomization. Randomization will take place in all study sites using an IWRS type of centralized system.

Randomization will be performed according to a ratio of 1:1 using minimization technique with stratification according to:centreTime to randomization: time between initiation of sunitinib and dose adjustment (<6 or ≥6 months)Heng prognostic factors at baseline (good and intermediate prognosis groups vs poor prognosis group)

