### Clinical measures

At treatment initiation (Fig. 3), data collected will include sociodemographic characteristics, oncologic history, symptoms at baseline, biological abnormalities, tumor assessment report, and evaluation of HRQoL (EORTC QLQ-C30 and EuroQoL EQ-5D questionnaires).

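### By-arm time to HRQoL deterioration is counted from inclusion against the pre-treatment score, so lasting deterioration that began before randomisation is dated to an arm not yet assigned

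*Protocol article*

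**What the plan says.** The section Analysis of HRQoL data gives one definition of TTD: "the time from inclusion in the study to a first significant deterioration in a HRQoL score as compared to the baseline score", completed by "with no further significant improvement, or death". The reference score is the one taken at treatment initiation (Clinical measures). Under Secondary endpoints the aim is "To estimate time to HRQoL deterioration (TTD) in each of the groups and in the overall population included in the study", so the same definition serves the randomised arms and the whole cohort.

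The arms do not exist at inclusion. Study design states: "At the inclusion, all patients start sunitinib at the recommended schedule 4/2 with sunitinib dosage of 50 mg once daily". Patients are randomised only "when a dosage adjustment (e.g., adverse event, patient request) of sunitinib is required". The minimisation factors include whether the time from sunitinib start to adjustment is below six months or at least six months, so the common period may be long.

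HRQoL is to be described "at baseline, at randomization, and every 6 weeks". The target dimensions for TTD are general health status, physical functioning, fatigue and pain. Each is to be shown by Kaplan-Meier curves and medians with 99% confidence intervals.

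**The concern.** Starting TTD at inclusion causes no difficulty in a trial that randomises at inclusion. In this trial randomisation comes later and is typically prompted by poor tolerance. Fatigue, pain and physical functioning may well worsen in the period that leads to it. If the worsening lasts, the definition dates the event to that period and places it in the curve of whichever arm was drawn afterwards.

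The persistence condition adds a second difficulty. An early drop stands as an event only if no significant improvement follows. For a randomised patient, much of the time in which improvement could occur is spent on the assigned schedule. An outcome of the arm therefore decides whether an event dated before the arm is counted.

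Preserved HRQoL is part of the main hypothesis stated under Study design, and TTD is the measure chosen to summarise HRQoL. A by-arm TTD that mixes the common period with the assigned schedule is hard to interpret in either direction.

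**Working it through.** **No TTD figure to reproduce.** The article gives no TTD rate, effect size or event count. Its only computed size (112 per arm) is for duration of treatment and does not bear on this point.

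**Logic from the text**

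1. The TTD clock starts at inclusion, and the arm is assigned later.
2. The reference score is taken at treatment initiation, before any adjustment.
3. A significant drop before randomisation with no later improvement meets the definition at the date of the drop.
4. The patient is then analysed in the randomised arm, so the event precedes assignment. This follows from the wording alone.

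**Illustration of size (all inputs assumed)**

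- Time to randomisation: exponential, mean 3 months.
- A share q of patients has a drop before randomisation, placed uniformly between inclusion and randomisation.
- A proportion r of these recover and then carry the same later hazard as other patients in their arm.
- Post-randomisation hazard: 0.12 per month on schedule 4/2 and 0.12 × 0.60 = 0.072 on schedule 2/1.
- Censoring at 36 months; Cox hazard ratio (HR) by arm; 1,000,000 simulated patients per setting.

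The early events that count are q × (1 − r). Counted from randomisation, the HR is 0.60 in every setting. Counted from inclusion:

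| Recovery 4/2 vs 2/1 | q = 30% | q = 50% | q = 70% |
|---|---|---|---|
| none | 0.71 | 0.78 | 0.86 |
| 40% vs 40% | 0.67 | 0.71 | 0.76 |
| 40% vs 60% | 0.62 | 0.62 | 0.61 |
| 40% vs 70% | 0.60 | 0.58 | 0.55 |

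As a check, q = 50% with 40% recovery in both arms leaves 0.50 × 0.60 = 30% counted. Its HR of 0.71 agrees with q = 30% and no recovery. With no early deterioration at all (q = 0) the HR from inclusion is already 0.61, because time to randomisation varies between patients. Smaller runs move these values by 0.01 to 0.02.

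**Separation before assignment.** Take q = 50% with recovery of 40% vs 60%. Counted early events are 0.50 × 0.60 = 30% vs 0.50 × 0.40 = 20%. At one month the event-free proportions are 0.820 vs 0.881, a gap of 0.061. Events dated before assignment supply 0.168 − 0.111 = 0.057 of that gap.

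**Medians.** From randomisation the true medians are ln 2 / 0.12 = 5.8 months and ln 2 / 0.072 = 9.6 months. From inclusion they are 9.0 vs 12.9 months with no early deterioration, and 3.3 vs 3.7 months with q = 50% and no recovery. The by-arm median can therefore lie above or below the time on the assigned schedule.

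**The case against.** The strongest defence is the persistence rule. A toxicity-led drop that resolves after the adjustment is not an event, and resolution on the assigned schedule is a real effect of the arm. A reader might infer that events before randomisation carry no information on the arms, so that the contrast must shrink towards no difference. The documents do not support that. With better recovery on schedule 2/1 the HR is hardly diluted, or not at all (third and fourth rows of the table). What remains is that such an effect is dated to a time before assignment.

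A reader might also infer bias in favour of one arm, or a TTD overstated by lead time. Neither follows. Randomisation balances the occurrence of early deterioration in expectation, and minimisation uses time to randomisation. Randomised patients cannot have died before randomisation, but they can have deteriorated, and early events shorten the median.

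The pre-treatment reference has merit. Scores at randomisation may already be depressed, which leaves less room to fall and hides failure to return to baseline. This stands, and it is why that reference should be kept in a sensitivity analysis.

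Consistency with the primary endpoint, also counted from sunitinib start, is a weaker defence. A patient being randomised is still on treatment, so a duration-of-treatment event cannot precede randomisation, whereas a TTD event can. The secondary endpoints also include a from-randomisation clock for treatment discontinuation but none for TTD.

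Finally, TTD is a secondary endpoint in a phase II trial that reports no P values. That limits the weight of the point.

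**Conclusion.** The point holds as a fault in the by-arm definition. Lasting deterioration that began before randomisation is charged to the arm assigned later, at a date before that arm existed. The curves can separate before assignment, and the by-arm medians do not describe time on the assigned schedule. This rests on the stated wording alone.

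The effect on the contrast is conditional. If recovery does not differ by arm, the contrast is diluted: from a true 0.60 to about 0.71 to 0.86 with no recovery, or 0.67 to 0.76 with 40% recovery in both arms. If recovery is better on schedule 2/1, the HR may hardly move (about 0.62 at 40% vs 60%) while events remain misdated. These figures rest on assumed rates and on the article's general intention to express treatment effect as an HR being applied to TTD. No size of dilution should be stated as fact.

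The inclusion clock suits the overall cohort. The article calls its definition the classical one and states no other for the arms; the full protocol was not available. The change is advisable but does not affect the primary analysis.

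**What to change.** - For the by-arm analysis, start TTD at randomisation and use the last score at or before randomisation as the reference.
- As a sensitivity analysis, report TTD from randomisation referenced to the pre-treatment score. State how patients already below that reference at randomisation are handled.
- Keep the inclusion-origin, baseline-referenced TTD as a description of the overall included population.

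The cost is a change of definition and a second reference score to report. HRQoL is already planned for description at randomisation and every six weeks. The schedule figure is not shown, so it is unclear whether a separate questionnaire is given at randomisation. If questionnaires come only on day 1 of each six-week cycle, the reference may be up to about six weeks old. Specifying the last score at or before randomisation covers both cases without new data collection.

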#### Analyses of safety

Analyses of toxicities will be performed on all randomized patients who received at least one dose of treatment and analyzed according to the treatment received. The toxicities will be graded according to the NCI CTCAE version 4.0 classification. All toxicities occurring after the first dose of drugs after randomization and after the inclusion will be described according to their grade. The time until toxicity grade 3–4 will be estimated using the Kaplan-Meier method.

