**Fig. 3 Fig3:**
[figure not shown]
Schedule of enrollment, interventions, and assessments in the SURF study

During each cycle of sunitinib before and after randomization (every 6 weeks), data collected will include symptoms and biological abnormalities, toxicities according to NCI CTCAE version 4.0, data related to sunitinib (start date, end date, dosage, dose modification and date, monitoring of compliance), toxicities related to sunitinib with grades according to NCI CTCAE version 4.0, and evaluation of HRQoL.

Tumor assessments will be performed every 12 weeks with evaluation of the response by RECIST 1.1 criteria.

During follow-up, cancer treatments provided later (start and end dates, type of treatment, reasons motivating the choice of treatment), the vital status and death-related data (date and cause), and the date and mode of progression for patients who left the study for reasons other than progression will be collected.

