#### Treatment duration

Patients participate until sunitinib is permanently discontinued for toxicity reason, progression, or death related to renal cancer or not.

The duration of follow-up after discontinuation of sunitinib will be 2 years. All death-related data will be collected as part of the study.

All patients included in this study can leave the study at any time, without having to justify the reason.

Study discontinuation include:Subject’s request to stop study treatment (withdrawal of consent)Decision of the investigatorTermination of the study by the sponsorAdverse eventsNon-compliance with the protocolProtocol-defined disease progressionLost to follow-upDeath

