### Statistics and data analysis

#### Sample size

The main objective of this randomized phase II trial is to evaluate the median DOT in each arm.

TThe following hypotheses will be tested: H0 (null hypothesis of inefficiency): median DOT of 6 months [15, 16] and H1 (alternative efficiency hypothesis): median DOT of 8.5 months. A Brookmeyer-Crowley type of test will be used to estimate the median. With a one-sided statistical test of significance (*α* 5%) and a power of 80%, it will be required to include 112 patients in each arm for 24 months with at least 12 months of follow-up.

The approximate upper critical value to reject H0 is 7.66 months. The number of patients is increased by 10% to take account of the potential progression or treatment discontinuation by patients before randomization and patients lost to follow-up. It will therefore be necessary to include 248 patients.

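### Toxicity before randomisation is described only in patients who are later randomised, a subset selected by a later event that itself depends on toxicity

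*Protocol article*

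**What the plan says.** The section Analyses of safety defines the set in one sentence: toxicity analyses are "performed on all randomized patients who received at least one dose of treatment", with patients classified by the treatment they received. It then gives the period covered: "All toxicities occurring after the first dose of drugs after randomization and after the inclusion will be described according to their grade". No other toxicity set is stated.

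Four other places bear on this:

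- Secondary endpoints lists the objective "To describe the toxicity before and after randomization". It names no population for toxicity.
- Study design says "At the inclusion, all patients start sunitinib at the recommended schedule 4/2", so exposure begins at inclusion and not at randomisation.
- Clinical measures says "During each cycle of sunitinib before and after randomization (every 6 weeks), data collected will include symptoms and biological abnormalities, toxicities", so the pre-randomisation data are collected.
- Treatment duration says "Patients participate until sunitinib is permanently discontinued for toxicity reason, progression, or death related to renal cancer or not". This is not confined to the period after randomisation. Sample size adds 10% to the number of patients "to take account of the potential progression or treatment discontinuation by patients before randomization" and for loss to follow-up.

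**The concern.** Before randomisation there are no arms. One regimen is given to everyone included, so the natural denominator for its toxicity is everyone who took it. The stated set instead keeps only those who later reach randomisation.

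Reaching randomisation is not neutral with respect to toxicity. The investigator must judge that an adjustment is needed, for example because of an adverse event or a patient request. The patient must also not already have stopped for good or died. Membership of the set is therefore decided by something that happens after the toxicity being described, and partly because of it.

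At stake is the pre-randomisation safety description. Under the stated rule it cannot contain a permanent stop for toxicity or a fatal toxicity before randomisation, although these are the most serious outcomes of that period. The Kaplan-Meier estimate of time to grade 3–4 toxicity in the same section falls under the same set.

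**Working it through.** **1. Who is in the set.** The possible courses of an included, treated patient, taken from Study design, Study procedures and randomization, Treatment duration and Sample size:

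| Course before randomisation | In the stated toxicity set? |
|---|---|
| Adjustment judged necessary, patient randomised | Yes |
| Permanent stop for toxicity | No |
| Death | No |
| Progression or another reason for stopping | No |
| Never needs an adjustment | No |

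In the stated set, the numbers of permanent stops for toxicity and of deaths before randomisation are therefore zero by construction.

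**2. The plan's own figure.** Inputs from Sample size: 112 per arm and a 10% increase.

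- 112 × 1.10 = 123.2, rounded up to 124 per arm.
- 2 × 124 = 248. The stated number is reproduced.

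**3. How many patients are left out.**

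- If 248 is the number included (Sample size) and 2 × 112 = 224 are randomised: 248 − 224 = 24, and 24/248 = 9.7%. At exactly 10%, the figure given in the Discussion, it is 248 × 0.10 = 24.8.
- If 248 is the number randomised (Study duration), the number to include depends on how the 10% is applied:
  - 248 × 1.10 = 272.8, rounded up to 273, so 273 − 248 = 25 left out (25/273 = 9.2%).
  - 248 / 0.90 = 275.6, rounded up to 276, so 276 − 248 = 28 left out (28/276 = 10.1%).

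The two sections disagree on what 248 counts. That is a separate matter, but it is why a range is given.

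**4. Direction and limit of the distortion.** Let q be the share never randomised, and let p_R and p_N be the proportions with a given pre-randomisation toxicity among the randomised and the never randomised. Then

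- p_all = (1 − q) × p_R + q × p_N
- p_R − p_all = q × (p_R − p_N)

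Both proportions lie between 0 and 1, so the reported figure can differ from the figure for all treated patients by at most q in either direction. That is about 9 to 10 percentage points on the values above. The documents give neither p_R nor p_N. Leaving out patients who stopped for severe toxicity lowers the reported toxicity, and leaving out patients who never needed an adjustment raises it. The sign of the net effect cannot be determined.

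**5. The dose condition.** Every randomised patient has already taken sunitinib. Read literally, the requirement of at least one dose excludes nobody. A patient randomised but not dosed afterwards would qualify, yet would have no post-randomisation treatment to be classified by.

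**The case against.** A reader might infer that the plan cannot meet its toxicity objective at all. The documents do not support that. The safety section explicitly covers toxicities after inclusion, so later-randomised patients are described in both periods. The PFS, OS and HRQoL-deterioration objectives name the overall included population, and the toxicity objective does not. A before-and-after description in randomised patients is thus a possible reading. This part of the objection stands and limits the point to a selected subset. It does not justify the selection, because the article gives no reason to describe a regimen taken by everyone in only some of them.

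A reader might also infer that the table must make the starting regimen look too safe, or that as many as half of the patients drop out of it because the abstract mentions dose modification in up to 50%. Neither follows. The net direction is open, as shown in the working. The 50% is a background statement about the standard schedule, whereas randomisation here rests on the investigator's judgement and may follow a patient request.

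Three further points stand:

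- The 10% in Sample size also covers progression and loss to follow-up, so the count of about 24 does not measure losses due to toxicity.
- Early deaths do not vanish from the trial: OS is estimated in all included patients and death data are collected. They are missing from the toxicity description only.
- The trial's aim is to assess schedule 2/1 after an adjustment. A randomised and treated set suits that purpose, and the section already names the first post-randomisation dose as a starting point. The dose condition therefore needs clearer wording, not a new design.

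**Conclusion.** The point holds in limited form. The article fixes one toxicity set for both periods, and for the pre-randomisation period that set is conditional on a later event that depends on toxicity. The objective is met for patients who are later randomised and not for the other treated patients.

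About 24 of 248 treated patients are left out, or about 25 to 28 if 248 is the number randomised. These counts assume that the protocol's 10% allowance is right and that all of it falls before randomisation, as the Discussion has it. The share due to toxicity is not given, and the net direction of bias is unknown.

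The primary duration-of-treatment analysis and the post-randomisation description by arm are unaffected. This should be corrected, but it does not threaten the trial's main result.

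**What to change.** In Analyses of safety, replace the single set by two:

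1. **Before randomisation:** all included patients with at least one dose of sunitinib, with toxicity counted from the first dose to randomisation or end of treatment. Report grade 5 events and permanent stops for toxicity in this set.
2. **After randomisation:** randomised patients with at least one dose after randomisation, by treatment received, with toxicity counted from that first dose.

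The cost is a sentence or two of text and one extra table. The data are already collected every cycle, so no additional patients or visits are needed.

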**Methods/design:**

SURF [NCT02689167] is a prospective, randomized, open-label phase IIb study. Patients are included at sunitinib initiation while receiving standard schedule 4/2 (50 mg daily) according to the marketing authorization indication. When a dose adjustment of sunitinib is required, patients are randomized between standard schedule 4/2 (37.5 mg daily) and experimental schedule 2/1 (50 mg daily). Key eligibility criteria are the following: patients with locally advanced inoperable or MRCC who are starting first-line treatment with sunitinib, with histologically or cytologically confirmed renal cancer clear cell variant or with a clear cell component, and with Karnofsky performance status ≥70%. The primary objective is to assess the median duration of sunitinib treatment (DOT) in each group. The key secondary objectives are progression-free survival, overall survival, time to randomization, objective response rate, safety, sunitinib dose intensity, health-related quality of life, and the description of main drivers triggering randomization. We hypothesized that experimental schedule 2/1 would result in an improvement in median DOT from 6 to 8.5 months. It was estimated that 112 patients would be needed in each arm during 24 months. In order to take into account the possibility of treatment discontinuation before randomization, 248 patients are necessary.

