**Fig. 1 Fig1:**
[figure not shown]
Trial design

The aim of this randomized clinical trial is to establish whether experimental schedule 2/1 is acceptable in terms of efficacy and toxicity. The main hypothesis is that experimental schedule 2/1 may maintain efficacy in terms of duration of treatment, survival rate, and response rate, has less toxicity, and preserves HRQoL.

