### Endpoint definitions

#### Primary endpoint

The primary objective of this study is to estimate the median duration of treatment (DOT) in each treatment group (arm 4/2 vs arm 2/1) calculated from sunitinib initiation (Fig. 2).

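### The by-grade toxicity summary makes no allowance for time on sunitinib outside the grade 3–4 Kaplan-Meier estimate, which biases all-grade, grade 1–2 and recurrent-event figures against the longer-treated arm

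*Protocol article*

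**What the plan says.** Under Analyses of safety, the safety population is all randomized patients with at least one dose, analysed by treatment received. The main summary is that "All toxicities occurring after the first dose of drugs after randomization and after the inclusion will be described according to their grade". The next sentence adds one time-based analysis: "The time until toxicity grade 3–4 will be estimated using the Kaplan-Meier method". Its time origin and censoring are not given.

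Under Clinical measures, the collection window is described by cycle: "During each cycle of sunitinib before and after randomization (every 6 weeks), data collected will include symptoms and biological abnormalities, toxicities". The items listed for follow-up are "cancer treatments provided later (start and end dates, type of treatment, reasons motivating the choice of treatment), the vital status and death-related data", together with progression for patients who left for another reason. Toxicity is not in that list.

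The Abstract hypothesizes that "experimental schedule 2/1 would result in an improvement in median DOT from 6 to 8.5 months". Under Primary endpoint, duration of treatment (DOT) is "calculated from sunitinib initiation", so it includes the time before randomization. Under Study design, the main hypothesis is that schedule 2/1 "may maintain efficacy in terms of duration of treatment, survival rate, and response rate, has less toxicity, and preserves HRQoL". The secondary objectives include a description of toxicity before and after randomization. They also include, separately, time from randomization to discontinuation and dose intensity by arm.

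**The concern.** Time on drug is the primary endpoint, and the trial is built on the expectation that arm 2/1 will have more of it. If toxicity is counted while patients take sunitinib, the arm that succeeds on the primary endpoint is also watched for longer and has more opportunity to record toxicity. A table of patients or events by grade, without a denominator in time, then mixes the toxicity rate with the length of observation.

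This bears on a stated hypothesis. Lower toxicity on 2/1 is part of the main hypothesis, and the Discussion wants side-effect data that can support using the schedule in practice. A real reduction in toxicity per month on drug could appear as no difference, or as a disadvantage.

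The before/after description has a related weakness. Time before randomization varies between patients (it is a minimization factor split at 6 months), and time after it depends on arm and on stopping. Crude counts for the two periods therefore cover unequal lengths of observation.

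**Working it through.** The article gives no toxicity rate and no toxicity figure, so there is nothing of the plan's own to reproduce. What follows is an illustration.

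**Inputs from the article.** Median DOT of 6 versus 8.5 months (Abstract; Sample size), counted from sunitinib initiation (Primary endpoint).

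**Assumptions.** Exponential time on drug; a constant toxicity rate r, equal in both arms; toxicity counted only while on drug; r from 0.02 to 0.40 per month.

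**Formulas.** For median time on drug m, the stopping hazard is h = ln 2 / m.
- Crude share of patients ever affected = r / (r + h)
- Mean events per patient = r / h
- Kaplan-Meier incidence at 6 months = 1 − exp(−6r)

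**Case A, medians 6 and 8.5 months.** h = 0.693/6 = 0.1155 and 0.693/8.5 = 0.0815 per month. At r = 0.10 the shares are 0.10/0.2155 = 46.4% and 0.10/0.1815 = 55.1%.

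| r per month | Arm 4/2 | Arm 2/1 | Difference (points) |
|---|---|---|---|
| 0.02 | 14.8% | 19.7% | 4.9 |
| 0.05 | 30.2% | 38.0% | 7.8 |
| 0.10 | 46.4% | 55.1% | 8.7 |
| 0.20 | 63.4% | 71.0% | 7.6 |
| 0.40 | 77.6% | 83.1% | 5.5 |

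Events per patient differ by the exposure ratio, 8.5/6 = 1.42. The 6-month Kaplan-Meier incidence is the same in both arms (45.1% at r = 0.10), and so is the rate per patient-month. The gap in the table therefore comes from exposure alone.

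**Case B, after randomization only.** DOT includes the time before randomization, while the arms can differ only after it. If randomization falls 3 months after initiation (an assumption), the medians after it are 6 − 3 = 3 and 8.5 − 3 = 5.5 months. Taking that remaining time as exponential, r = 0.10 gives 30.2% versus 44.2%. Over r = 0.02 to 0.40 the gap is 5.7 to 14.9 points, and the event ratio is 5.5/3 = 1.83.

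**When the gap closes.** Let the arms have different rates. Crude shares are equal when r/h is equal, that is, when the 2/1 rate divided by the 4/2 rate is 6/8.5 = 0.71 (Case A) or 3/5.5 = 0.55 (Case B). In Case A a true reduction of 1 − 0.71 = 29% would show as no difference. Below that ratio the direction reverses: with 0.10 per month on 4/2 and 0.05 on 2/1, the table gives 46.4% versus 38.0%.

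**The case against.** The strongest reply is that this is a condensed article and that exposure-adjusted tables are ordinary content of an analysis plan that is not shown. That plan may well contain them. The article is not silent, however: it names its summary of toxicity, and that summary suits the stated hypothesis poorly.

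Four stronger readings are tempting, and the document does not support them.
- A reader might infer that toxicity is described with no regard to time at all. The grade 3–4 Kaplan-Meier sentence rules that out, and with suitable censoring it removes the exposure effect for severe toxicity.
- A reader might infer that arm 2/1 must look worse by construction. It need not: a sufficiently lower 2/1 rate offsets or reverses the bias, and the trial expects a lower rate.
- A reader might infer that toxicity is recorded only during cycles. The article never says only, and the safety section sets no end to the window. The inference rests on what the follow-up list contains, and the full protocol may say more.
- A reader might infer that the before/after difference will be taken as an effect of the schedule. No text does so; the objective is descriptive.

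It is also fair that no between-arm safety test is planned, that cumulative toxicity is a legitimate question, and that exposure is reported elsewhere. Reporting time on drug separately shows that exposure differed, but it does not adjust the toxicity table.

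Finally, the model treats toxicity and stopping as independent, although toxicity is a listed reason for stopping (Treatment duration). That criticism stands: the sizes are illustrative.

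**Conclusion.** The concern holds in limited form. For all-grade, grade 1–2 and recurrent toxicity, the article commits to a crude by-grade summary while expecting unequal time on drug. That biases the comparison against the longer-treated arm and can mask the hypothesized advantage of 2/1. The size is about 5 to 9 points in the share of patients affected, and a factor of 1.42 in events per patient, when rates are equal. It is about 6 to 15 points and 1.83 if 3 months precede randomization. These figures rest on assumed rates, exponential time on drug, stopping that does not depend on toxicity, and a toxicity window that follows time on drug. The direction is a tendency, not a certainty. Grade 3–4 toxicity is covered in principle by the Kaplan-Meier estimate, provided that its origin and censoring are set suitably.

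**What to change.** In Analyses of safety, add the following for every grade group, by arm and after randomization, beside the crude by-grade table:
- events, and patients with a first event, per patient-month (or per 6-week cycle) on sunitinib; or
- incidence over the same fixed window after randomization in both arms.

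Base any between-arm statement on toxicity on these figures, together with the grade 3–4 Kaplan-Meier estimate taken from randomization with its censoring rule stated. Give the before/after description per unit of time on drug as well.

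The cost is some wording and a few extra tables. Sunitinib start and end dates are already collected under Clinical measures, so no new data are needed. Rates per patient-month assume a roughly constant hazard; the fixed-window figure covers that weakness, so showing both is the safer choice.
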